### Randomisation

Figure 1 shows the expected flow of participants throughout the study. Consenting participants will be randomised in a 2:1 ratio through computer-generated randomisation after completing the T1 assessment. Randomisation will be guaranteed by a third researcher (different from the two responsible for enrolment and allocation of the participants to the EG-KindMap and WL-CG groups) who will only know the participants’ code. Participants randomised into KindMap-EG will be stratified into a Portuguese or English-speaking group. All participants will be informed of the randomisation results.

**Figure 1 F1:**
[figure not shown]
Participant flowchart.

### Intervention

The KindMap is a stand-alone, cost-free e-mental health tool presenting a low-intensive psychological intervention to be used at users’ own time and pace. The KindMap intervention is described using the Template for Intervention Description and Replication.^38^

The KindMap web app was developed by a multidisciplinary research team following the framework commissioned by the Medical Research Council and the National Institute of Health Research for developing complex interventions^39 40^ and a User-Centred Design methodology. This intervention was derived from adapting the MBPI’s content to a web app format. The MBPI contents were developed based on the Contextual Cognitive-Behavioural Therapies (CCBT) framework, incorporating mindfulness, self-compassion and ACT components.

The KindMap will be available in European Portuguese and English at www.kindmap.pt. KindMap’s landing page will provide the background and aims of the intervention, the target audience, a summary of the contents of its eight modules and a brief presentation of the KindMap team. As a stand-alone tool, the KindMap can be simultaneously and freely accessed by any number of interested people and used at users’ convenience time and pace. For the duration of the feasibility study, only participants meeting eligible criteria will have access to the KindMap. It is a completely self-guided web app, with no human support, but a support contact list will be provided. For technical problems, an email address will be available.

The KindMap comprises eight modules addressing psychoeducation, mindfulness and compassion-guided practices, and ACT-based experiential exercises (table 1). Each module is structured to heighten understanding of a specific subject and cultivate a particular therapeutic skill (figure 2). The modules’ contents are delivered through text, video, audio, experiential exercises, prompts for reflection and interactive content to promote users’ engagement (figure 3). The recommendation is to address a module per week, leading to 8 weeks of using the KindMap.

**Table 1 T1:** KindMap modules, contents, practices and exercises

Module		Contents	Practices and exercises
1	KindMap: The Beginning	Life areas affected by infertilityThe psychological impact of infertilityThe concept of mindfulnessDifficulties in the mindfulness practiceMindfulness practice instructions	*Meditation practice—The three-minute breathing spaceMeditation practice—Being in the present moment*
2	Being mindful of your mind’s work	Being in the present momentHow the mind and emotions workSimple ways of being present	*Experiential exercise—Being in the present momentMeditation practice—Body Scan*
3	Choosing your values	How the mind worksPassengers on the bus metaphorValues clarification	*Meditation practice—Sounds and thoughts meditationExperiential exercise—Values identification/clarification*
4	Being kind to yourself and taking good care	Lifestyle considerations—eating, physical exercise, alcohol, nicotine, sleep, relationships,Self-careSelf-compassion	*Experiential exercise—The time pieMeditation practice—Compassion mindfulnessExperiential exercise—Compassionate postcardMeditation practice—Moment of self-compassion*
5	Being open to give and receive compassion	Interpersonal relationshipsDealing with other people’s commentsThe impact of infertility on the coupleCompassion for others and receiving compassion from others	*Meditation practice—Giving and taking meditationExperiential exercise—Dyad communication*
6	Recognise and allow	Be an explorer on the expedition of your mindAcceptanceThe pain in my headTo live the experience as it is	*Meditation practice—Leaves on a streamMeditation practice—Exploring difficultyExperiential exercise—The pain in my head*
7	Get into your life	Dealing with challenges and obstaclesGoose in the bottle enigmaCommitted action	*Experiential exercise—Obstacles in the riverChallenge—Goose in the bottle enigmaMeditative practice—Being where you are*
8	You’re not alone in this road	Facing the challenge of infertilityPeople dealing with infertility testimonies	*Meditative practice—Brief loving-kindnessMeditative practice—Mindfulness: being present*

Note: Every KindMap module starts with a brief theme introduction and ends with a gentle reminder quote and a module summary. At the end of each module, practices and exercises are suggested to be completed until the next module.

**Figure 2 F2:**
[figure not shown]
KindMap logic model.

**Figure 3 F3:**
[figure not shown]
KindMap screenshots of the mobile app.

After completing each module, users unlock the following module and have automatic access to the ‘Practices’ section activities/meditations to practice between modules. The final topic addressed is a wrap-up of the programme designed to encourage users to recognise the changes they have undergone since the first module, acknowledge the therapeutic skills they have acquired/developed and motivate them to incorporate these skills in their everyday lives and upcoming difficult situations.

Every time users access the web app, they are invited to answer two brief questions about their well-being state and state of mindfulness (present moment awareness), using a 10-point Likert scale ranging from *not at all* (1) to *very/strongly* (10).

There will be no special criteria for discontinuing or modifying allocated interventions.

### Measures

At baseline (T1), sociodemographic and clinical information will be collected (eg, gender, age, marital status, infertility type and cause, previous fertility treatments and former psychological counselling) combined with standardised self-report measures of well-being, infertility-related stress, depression and anxiety. These self-report measures will also be completed at T2 and T3. Additionally, at T2, the feasibility questionnaire regarding the KindMap intervention and the study protocol will be completed by the KindMap-EG participants.

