### Procedures

On registering on the KindMap landing page, participants will be asked to complete a questionnaire addressing the eligibility criteria. Participants who meet the eligibility criteria will receive an email containing detailed information about the study and a link to an online platform where they will be asked to provide informed consent (using several mandatory checkboxes) and then proceed to complete the T1 assessment. After T1, consenting participants will be randomly allocated to the KindMap-EG or WL-CG. KindMap-EG participants will have immediate access to the KindMap web app; 8–10 weeks after the baseline, all participants will be invited to complete the T2 assessment by email. At this moment, participants in the WL-CG will be given access to the KindMap web app. 10 weeks later (T3), participants in the KindMap-EG will be invited to complete the T3 assessment. Participants not completing assessments (T1, T2 or T3) will receive reminder emails on days 3, 6 and 9. After receiving the reminders, participants who have not completed the assessment will receive a brief exit questionnaire inquiring about the reasons for withdrawal. The assessment protocols will be hosted on Limesurvey.

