### Sample size

G*Power calculations for within-between interaction Analysis of Variance (ANOVA) repeated measures (two-conditions, two-time points), assuming a p=0.05, effect size *f*=0.25, power=0.95, recommend a sample size of 54. Assuming participation and retention rates of 60% and 34% (observed in similar apps), we will recruit n=180 participants. This sample size is in accordance with Sim and Lewis^37^ recommendation of at least 50 participants for feasibility studies.

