#### Feasibility outcomes

Aligned with Bowen *et al*,^35^ the current study uses several feasibility dimensions to evaluate the KindMap intervention and study protocol. For the KindMap intervention, demand, adaptation, acceptability, implementation, practicality, integration and limited efficacy dimensions will be assessed.

Demand will be assessed by programme adherence (eg, number of users and percentage of modules completed). Adaptation will be assessed by the differences in the hours spent and total number of visits of participants engaging with the KindMap in Portuguese and English. Acceptability will be assessed by user-reported programme satisfaction, perceived usefulness of each module and meditation practices and willingness to recommend the KindMap to peers. Implementation will be assessed by responses to open-ended questions regarding technical problems, the suitability of the 8-week recommended engagement period and barriers and facilitators of use. Practicality will be assessed by the number of participants who use the KindMap as intended (complete eight modules), complete six out of eight modules during the 8–10-week recommended engagement period, and the time taken to use the web app as intended. Integration will be assessed by participants’ perception of using the KindMap skills in everyday life and their willingness to continue doing so. Limited efficacy will be assessed by the effect size estimations of primary and secondary self-reported outcomes changes in the EG-KindMap versus WL-CG. More specifically, Modified Intention-to-Treat (mITT, all participants randomised) and Per-Protocol (PP, only participants who received a sufficient dose) analyses on primary (well-being) and secondary outcomes (infertility-related stress, depression and anxiety) measured at T1, T2 and T3 will be performed.

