For the study protocol, feasibility dimensions of demand, acceptability, implementation, practicality and adaptation will be evaluated. Demand will be assessed by participation and retention rates and reasons for non-participation/withdrawal; acceptability will be addressed by the proportion of participants who completed T1, T2 and T3 assessment moments; implementation by the reported issues concerning study procedures or materials; practicality by the time taken to complete assessments and adaptation by the participation and attrition rates according to the chosen language version of the KindMap. A traffic-light progression criteria will be used for each feasibility outcome.^41^

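### User-reported acceptability of KindMap is collected once, from those who still answer at T2, so it is likely to over-represent people who persisted

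*Protocol article*

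**What the plan says.** The feasibility questionnaire has one time point and one arm. The Measures section of the protocol article states that "at T2, the feasibility questionnaire regarding the KindMap intervention and the study protocol will be completed by the KindMap-EG participants".

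For the intervention, the Feasibility outcomes section defines the dimension entirely by self-report: "Acceptability will be assessed by user-reported programme satisfaction, perceived usefulness of each module and meditation practices and willingness to recommend the KindMap to peers". Implementation (open-ended questions) and integration (perceived use of the skills) are self-reported too. The same section says that a traffic-light criterion applies to every feasibility outcome.

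For the study protocol, the same word means something else: "acceptability will be addressed by the proportion of participants who completed T1, T2 and T3 assessment moments".

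On expected loss, the Sample size section says: "Assuming participation and retention rates of 60% and 34% (observed in similar apps), we will recruit n=180 participants". It does not say at which assessment, or in which arm, the 34% applies.

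For people who do not complete an assessment, the Procedures section provides reminders on days 3, 6 and 9. After these, those still silent "will receive a brief exit questionnaire inquiring about the reasons for withdrawal". The Feasibility outcomes section places reasons for withdrawal under demand for the study protocol, not under acceptability of the intervention. The Intervention section describes two short questions at each log-in, on well-being and on present-moment awareness, and says that each module opens only when the previous one is finished.

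**The concern.** People who dislike an unguided app can be expected to stop using it, and people who stop using it are less likely to answer a survey about it 8–10 weeks later. Part of the selection is built in: because modules open in sequence, an informed rating of a late module can come only from someone who reached it.

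The Objectives section makes acceptability a study question, asking whether the stand-alone online format will be as acceptable as the in-person programme, and expects the results to guide improvements to the app. The views most useful for that purpose belong to those who left. If acceptability looks good beside poor retention, the team cannot tell whether to change the content or merely the follow-up procedures. This is a data-collection choice, so no later analysis can recover ratings that were never asked for.

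**Working it through.** **1. The plan's own figure.** The Sample size section gives "power=0.95, recommend a sample size of 54" for a two-group, two-time interaction with f = 0.25 and alpha 0.05. Taking a correlation of 0.5 between the two measurements (not stated in the article, assumed here):

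- noncentrality = f² × N × m / (1 − ρ) = 0.0625 × 54 × 2 / 0.5 = 13.5, with 1 and 52 degrees of freedom
- power = 0.9501, so N = 54 reproduces.

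The recruitment target does not follow from the quoted rates: 54 / 0.34 = 159 and 54 / (0.60 × 0.34) = 265, against 180. That is a separate matter. Here it means only that the role of the 34% is unclear, so both readings of the 180 are carried forward.

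**2. Expected questionnaire respondents in KindMap-EG**, with 2:1 allocation and 34% answering at T2:

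| Reading of 180 | Randomised | KindMap-EG | Respondents | Silent |
|---|---|---|---|---|
| 180 randomised | 180 | 180 × 2/3 = 120 | 120 × 0.34 = 40.8 | 79.2 |
| 60% of 180 take part | 108 | 108 × 2/3 = 72 | 72 × 0.34 = 24.5 | 47.5 |

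Randomisation follows consent and T1, so if participation removes people first, the smaller respondent count belongs to 72, not to 120.

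**3. Effect on the acceptability percentage.** Let s_R and s_N be the proportions satisfied among responders and non-responders.

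- all allocated = 0.34 × s_R + 0.66 × s_N
- responder figure minus all allocated = 0.66 × (s_R − s_N)

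The difference is zero if the two groups do not differ. Neither proportion is in the documents. With s_R = 0.80 as an assumption:

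| s_N (assumed) | All allocated | Overstatement (points) |
|---|---|---|
| 0% | 27% | 53 |
| 40% | 54% | 26 |
| 60% | 67% | 13 |
| 80% | 80% | 0 |
| 100% | 93% | −13 |

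**4. How strong is the 80%/40% example?** It implies a response rate of 0.272 / 0.536 = 51% among satisfied users and 0.068 / 0.464 = 15% among the others, a ratio of about 3.5. A milder case: half of all users satisfied, and satisfied users twice as likely to answer. The response rates are then 45% and 23%, and the responder figure is 0.5 × 0.453 / 0.34 = 67%, an overstatement of 17 points.

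**5. If the 34% were attrition rather than retention.** With 66% answering, the same 80% and 40% give 0.66 × 0.80 + 0.34 × 0.40 = 66%, an overstatement of 14 points; the bounds are 53% and 87%. The issue shrinks but remains.

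**6. Do other provisions supply the missing ratings?**

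- Exit questionnaire: reaches the right people, but is described as asking for reasons for withdrawal, and those reasons feed demand for the study protocol.
- In-app questions: well-being and present-moment awareness, not satisfaction.
- Adherence, practicality and retention: count those lost, but do not record what they thought of the app.

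**The case against.** The strongest reply is that progression does not rest on satisfaction alone. Retention, modules completed, use as intended and assessment completion are separate outcomes, each with its own traffic light, and heavy loss would show in them directly. Study-protocol acceptability is itself a completion proportion. This stands, and it limits the consequence. A reader might infer that the acceptability result will certainly be biased, that most allocated users may find the app unacceptable while the light turns green, and that a wrong progression decision follows. The documents do not support that. They give no satisfaction rates for either group, no rule by which satisfaction decides alone, and no link between the 34% and T2 or this arm. A wrong decision is possible, not expected.

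A second reply is that the exit questionnaire goes to exactly the missing group and that stated reasons may include disliking the app. This stands in part: it could reveal some dissatisfaction. As described, though, it yields reasons rather than ratings, and they are counted elsewhere.

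A third reply is that the article gives no denominator or cut-offs and may leave them to a fuller document. That is fair, and their absence is not criticised here. The point is what is asked, of whom and when, which the article does fix.

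Finally, the patient and public involvement statement says that professionals and potential users will have their experiences explored at the next stage. It does not describe these as trial participants who stopped, so it does not fill the gap.

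**Conclusion.** The concern holds for user-reported acceptability of the intervention, and only for that dimension. As written, the plan obtains it once, from those who answer at T2, with no described satisfaction measure for the rest. The result is likely to lean towards people who persisted. The direction is a reasonable inference; the size is unknown. Under the assumed 80% and 40% it is 26 points, under the milder selection above 17 points, and it is nil if responders and non-responders agree. The respondent counts rest on reading the 34% as retention at T2 in KindMap-EG. This is a cheap improvement worth making, not an error that undermines the study.

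**What to change.** 1. Add a one-item satisfaction or usefulness rating in the app at the end of each module. People who later stop then still contribute ratings of the modules that they completed. Late modules will still be rated only by those who reach them.
2. Add one satisfaction item to the existing exit questionnaire and keep its present timing after the day-9 reminder. Placing its link in the earlier reminders could draw people away from completing T2.
3. Report the responder percentage together with the number allocated to KindMap-EG, give best- and worst-case bounds for non-responders as a sensitivity analysis, and read the acceptability traffic light alongside them. Do not apply the light to a figure that counts every non-responder as dissatisfied: at 34% response it could never exceed 34%, so it would largely measure retention again.

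The cost is a small app change, slight user burden and a less flattering figure. Those who stop before finishing module 1 and ignore the exit questionnaire will remain unmeasured.

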#### Feasibility outcomes

Aligned with Bowen *et al*,^35^ the current study uses several feasibility dimensions to evaluate the KindMap intervention and study protocol. For the KindMap intervention, demand, adaptation, acceptability, implementation, practicality, integration and limited efficacy dimensions will be assessed.

Demand will be assessed by programme adherence (eg, number of users and percentage of modules completed). Adaptation will be assessed by the differences in the hours spent and total number of visits of participants engaging with the KindMap in Portuguese and English. Acceptability will be assessed by user-reported programme satisfaction, perceived usefulness of each module and meditation practices and willingness to recommend the KindMap to peers. Implementation will be assessed by responses to open-ended questions regarding technical problems, the suitability of the 8-week recommended engagement period and barriers and facilitators of use. Practicality will be assessed by the number of participants who use the KindMap as intended (complete eight modules), complete six out of eight modules during the 8–10-week recommended engagement period, and the time taken to use the web app as intended. Integration will be assessed by participants’ perception of using the KindMap skills in everyday life and their willingness to continue doing so. Limited efficacy will be assessed by the effect size estimations of primary and secondary self-reported outcomes changes in the EG-KindMap versus WL-CG. More specifically, Modified Intention-to-Treat (mITT, all participants randomised) and Per-Protocol (PP, only participants who received a sufficient dose) analyses on primary (well-being) and secondary outcomes (infertility-related stress, depression and anxiety) measured at T1, T2 and T3 will be performed.

For the study protocol, feasibility dimensions of demand, acceptability, implementation, practicality and adaptation will be evaluated. Demand will be assessed by participation and retention rates and reasons for non-participation/withdrawal; acceptability will be addressed by the proportion of participants who completed T1, T2 and T3 assessment moments; implementation by the reported issues concerning study procedures or materials; practicality by the time taken to complete assessments and adaptation by the participation and attrition rates according to the chosen language version of the KindMap. A traffic-light progression criteria will be used for each feasibility outcome.^41^

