**Methods and analysis:**

A two-arm 2:1 non-blinded feasibility randomised controlled trial (RCT) will be conducted. Participants are people dealing with infertility, who are able to access the Internet and understand Portuguese or English. Consent participants will complete an online survey at 3-time assessment moments. After baseline assessment, participants will be randomised into the KindMap experimental group (KindMap-EG; with immediate access to the web app) or the waiting-list control group. The primary outcome is well-being (WHO Index-5); secondary outcomes are infertility-related stress (Fertility Problem Inventory—Short Form), anxiety and depression (Patient Health Questionnaire for Depression and Anxiety-4); mindfulness (Five Facet Mindfulness Questionnaire—Short Form), self-compassion (Self-Compassion Scale—Short Form), psychological flexibility (Psy-Flex) and infertility-related self-efficacy are the potential mechanisms of change. KindMap-EG will also complete a feasibility survey.

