## Methods and analysis

### Study design

A two-arm, parallel-group, non-blinded feasibility study with 2:1 computer-generated randomised allocation (www.random.org) to the KindMap experimental group (KindMap-EG; prompt access to KindMap web app) or waiting-list control group (WL-CG; access to KindMap after 10 weeks). The study will encompass three assessment moments: baseline (T1; pre-intervention), 8–10 weeks after baseline (T2; post-intervention) and 10 weeks after post-intervention (T3; only for KindMap-EG). Although there is a recommendation for completing a module per week (similar to the MBPI sessions), the KindMap may be used at the participant’s own pace. Therefore, T2 will occur considering a 2-week flexible period. A T3 assessment will also be implemented at a 10-week interval.

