### Data analysis plan

Statistical analysis will be conducted using IBM SPSS Statistics V.27. Descriptive statistics will be performed. Specifically, for the continuous variables, means and SD or SE of the mean will be obtained, and for categorical variables, absolute numbers and percentages (%) will be calculated. Differences between groups will be assessed through t*-*tests and χ^2^ tests. mITT (all participants who will complete T1 and T2) and PP (only participants who will receive a sufficient dose) analyses on primary (well-being) and secondary outcomes (infertility-related stress, depression and anxiety) measured at T1, T2 and T3 will be performed to explore limited efficacy on the study outcomes.

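### T3 is collected only in KindMap-EG, but the plan places it inside the between-arm efficacy assessment and inside an acceptability proportion that, read plainly, cannot exceed 66.7%

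*Protocol article*

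**What the plan says.** **Who is assessed at T3.** The protocol article's Study design section places the third assessment "10 weeks after post-intervention (T3; only for KindMap-EG". The Procedures section agrees: "10 weeks later (T3), participants in the KindMap-EG will be invited to complete the T3 assessment". It also says of the T2 time point: "At this moment, participants in the WL-CG will be given access to the KindMap web app".

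**Efficacy.** Under Feasibility outcomes, "Limited efficacy will be assessed by the effect size estimations of primary and secondary self-reported outcomes changes in the EG-KindMap versus WL-CG". The next sentence makes this specific: modified intention-to-treat (there, everyone randomised) and per-protocol analyses of the primary and secondary outcomes at all three assessments. The Data analysis plan repeats the three time points ("measured at T1, T2 and T3 will be performed to explore limited efficacy on the study outcomes"), but there the modified intention-to-treat set is those who complete T1 and T2.

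**Acceptability of the study protocol.** Also under Feasibility outcomes, "acceptability will be addressed by the proportion of participants who completed T1, T2 and T3 assessment moments". Traffic-light progression criteria are to be applied to every feasibility outcome.

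**Other places.** The abstract says "Consent participants will complete an online survey at 3-time assessment moments". The opening paragraph of Measures likewise has the self-report measures repeated at T2 and T3 without naming an arm. On allocation, the Randomisation section says: "Consenting participants will be randomised in a 2:1 ratio through computer-generated randomisation after completing the T1 assessment".

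**The concern.** The design gives T3 to one arm, while two stated measures are worded as if both arms had it.

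For efficacy, the sentence that specifies the comparison of KindMap-EG with WL-CG includes T3. Followed literally, it asks for a contrast with no control data. WL-CG has also had the app since T2, so it would no longer be an untreated comparator by then. The risk is that change within KindMap-EG up to T3 is reported under a heading that promises a controlled comparison.

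For acceptability, about one third of randomised participants cannot meet the criterion, because they are never invited to T3. The measure then mixes willingness to complete assessments with the allocation ratio. It feeds a traffic-light rule, and the Discussion says those criteria will help decide whether a future trial is worth conducting.

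**Working it through.** **1. The plan's own figure.** The Sample size section gives N = 54 for a within-between interaction in a repeated-measures ANOVA with two conditions and two time points, α = 0.05, f = 0.25 and power 0.95.

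- Formula: λ = f² × N × m / (1 − ρ), df1 = (k − 1)(m − 1), df2 = (N − k)(m − 1), with k = 2 groups and m = 2 time points.
- The correlation ρ is not stated. Assuming ρ = 0.5: λ = 0.0625 × 54 × 2 / 0.5 = 13.5, df1 = 1, df2 = 52, power = 0.9501. At N = 53 the power is 0.9464, so 54 is reproduced.
- Range over the assumption, in steps of two participants: ρ = 0 needs 106, ρ = 0.3 needs 76, ρ = 0.7 needs 34.

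What matters here is that the sample-size model has two time points. It fits a T1–T2 comparison of two arms, and T3 plays no part in it.

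**2. Data available for a between-arm contrast.**

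| Assessment | KindMap-EG | WL-CG | Randomised contrast possible? |
|---|---|---|---|
| T1 | yes | yes | baseline |
| T2 | yes | yes, access to the app starts here | yes |
| T3 | yes | not invited, 0 observations | no |

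No choice of model changes the last row. The contrast is not identified without control data.

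**3. Ceiling on the acceptability proportion.** Take all randomised participants as denominator and require all three assessments. Only KindMap-EG can qualify, so with completion c in that arm the reported figure is (2/3) × c. The maximum, at c = 1, is 2/(2 + 1) = 66.7%. It does not depend on the number randomised: 120/180, 72/108 and 36/54 all give 66.7%.

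| Completion of all three in KindMap-EG | Reported over all randomised |
|---|---|
| 100% | 66.7% |
| 90% | 60.0% |
| 80% | 53.3% |
| 60% | 40.0% |
| 34% | 22.7% |

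The 34% row uses the retention rate that the Sample size section assumes.

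**4. Other denominators.**

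- All who consented: randomisation follows T1, so this number is at least as large as the number randomised, and the ceiling is 66.7% or lower.
- Each assessment scored separately over all randomised: T1 is 100% by construction, T2 has no ceiling, and only T3 is capped at 66.7%.
- KindMap-EG only at T3: no ceiling.

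**The case against.** The strongest reply is that the plan already implies the right analysis. The sample-size model has two time points, the Data analysis plan builds its modified intention-to-treat set from T1 and T2, and Study design restricts T3. Saying that outcomes are analysed at three assessments is also true if one arm contributes three and the other two. The Data analysis plan names no between-arm contrast at T3. The acceptability sentence could mean completion at each assessment among those invited, since listing T1 adds nothing for people randomised after T1. An abstract may also use shorthand.

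Much of this stands, and it rules out several stronger readings.

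- A reader might infer that the between-arm efficacy analysis as a whole lacks control data. It does not: the T1–T2 contrast has both arms.
- A reader might infer that a three-time-point repeated-measures ANOVA would delete every control listwise. The article plans no such model. SPSS is named, but the only ANOVA is the two-time-point one used for sample size.
- A reader might treat 180 as the number randomised. It is the recruitment target. The ceiling depends only on the allocation ratio.
- A reader might infer that the progression decision will be wrong. The article gives no cut-offs, so that cannot be shown, and their absence from a condensed article is not a fault.

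Two things remain. Under Feasibility outcomes, the three-assessment analysis is offered as the specification of the comparison with WL-CG, in all randomised. The acceptability proportion refers to participants without naming an arm, in a paragraph about the study protocol, which covers both arms. The article does name KindMap-EG where it means that arm alone, as it does for the feasibility questionnaire.

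**Conclusion.** The point holds in a limited form. The T1–T2 between-arm effect size is sound. A T3 between-arm effect size has no control observations and cannot be estimated, yet the text that specifies the between-arm assessment includes T3.

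On the plain reading, the acceptability proportion is capped at 66.7% and understates completion in KindMap-EG by one third; for example, 90% becomes 60%. This rests on three assumptions: both arms in the denominator, completion of all three assessments required, and a realised split close to 2:1. The article does not spell out the first two. If T3 was meant to be counted over KindMap-EG alone, the ceiling disappears, but the text needs to say so.

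This is a correction that should be made before the results are scored. It does not invalidate the study.

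**What to change.** - **Feasibility outcomes (limited efficacy) and Data analysis plan:** restrict the KindMap-EG versus WL-CG effect size to T1–T2. Report T3 as uncontrolled follow-up within KindMap-EG, with a confidence interval and no between-arm claim.
- **Feasibility outcomes (acceptability of the study protocol):** replace the single proportion with T2 completion over all randomised, shown by arm, and T3 completion over KindMap-EG only. Apply the traffic-light rule to those figures, and check any cut-off already set for the combined proportion against the new denominators.
- **Abstract and the opening of Measures:** add that T3 applies to KindMap-EG only.

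The cost is wording. No data collection, sample size or visit changes, and the sample-size model already fits the T1–T2 contrast.
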